## Abstract

**Background:**

Life after stroke can be an ongoing struggle with over half of all survivors reporting unmet emotional and social needs. In the United Kingdom’s (UK) national clinical guidelines for stroke, self-management is suggested as one approach which can support long-term needs. In the UK NHS, self-management interventions are delivered in various ways. Regardless of the delivery mechanism, a tailored approach and ways to integrate peer support are advocated. Group delivery offers a platform for peer support and has the potential to remain individualised. However, before the efficacy of a group self-management intervention can be tested, the feasibility must be explored. This research investigates the feasibility of a GroUp Self-management intervention for sTrOke (GUSTO).

**Methods:**

A randomised waitlist control design will be used to investigate the feasibility of a group self-management intervention adapted from an existing one-to-one intervention called *Bridges*. A mixed methods approach will be used. Qualitative work will capture participant experience, while quantitative work will allow preliminary comparison between the intervention and waitlist groups (between subjects) and pre-post intervention measures (within subjects). Interviews will be conducted with stroke survivors and focus groups with family and friends to assess acceptability of the intervention.

**Discussion:**

There is a growing interest in group-based self-management interventions for stroke as a method of supporting stroke survivors’ ongoing unmet needs. This is an area with limited research to date. This study will inform design of a fully powered trial which would assess the efficacy of a group self-management intervention following stroke.

**Trial registration:**

ISRCTN19867168

**Electronic supplementary material:**

The online version of this article (10.1186/s40814-017-0220-1) contains supplementary material, which is available to authorized users.

## Background

At present, there are 1.2 million people living with the effects of stroke in the UK [1]. These effects are varied, but over three quarters of survivors report limb weakness, half report unmet needs relating to social and emotional issues and a third report a communication disorder [1, 2]. The long-term nature of these effects has led to suggestions that stroke should be defined as a chronic disease albeit one that starts with an acute event [3]. Although there have been improvements in acute care services, once care ends many stroke survivors feel ‘abandoned’ [4] and perceive living with stroke as an ‘ongoing struggle’ [5]. The ‘alarming neglect’ in the development of services available to survivors in the long term has been noted, and there is a call for better long-term support [3, 6].

In order to improve support for individuals living with chronic diseases such as stroke, health care professionals need to ‘abandon’ traditional ways of thinking [6]. Current services often place high expectation on the individual to manage and take responsibility for their condition [4, 7], which can result in significant variation in the extent to which survivors are supported to manage life after stroke [8]. New approaches are needed, for example, one way of supporting survivors increasingly recognised by national policy is a tailored self-management approach [9]. Broadly speaking, self-management supports individuals ‘to manage their health on a day-to-day basis’ [10], through increasing an individual’s belief in their own ability to engage with specific tasks [11].

Self-management interventions specifically for stroke are relatively new. It is thought they have emerged after the success of interventions such as the Stanford Chronic Disease Self-Management Programme which has been implemented for a range of chronic conditions [12]. Although chronic conditions vary greatly in presentation, there are a number of similarities in the way they are managed which suggests similar strategies could be applied to stroke [13]. A recent Cochrane review explored self-management interventions specifically for stroke and found significant effects in favour of the self-management interventions for both quality of life and self-efficacy [14]. Despite their variability in the delivery of the interventions, those based on the concept of self-efficacy showed most promise.

One example of a self-management intervention, based on self-efficacy and currently integrated into some stroke teams within the UK’s National Health Service, is *Bridges self-management or Bridges* [15]. Bridges is underpinned by self-efficacy principles and offers a unified way of working for stroke teams which enables flexibility through context adaption such as the setting or time post stroke, ensuring the content remains tailored and personalised. The intervention is currently delivered on a one-to-one basis; however, the notion that self-management is an ‘individual construct’ is questioned with some suggesting self-management is a ‘collective process where social networks can potentially make a considerable contribution to improving health outcomes’ [16]. Evidence for this comes from stroke survivors themselves who report the degree to which their self-manage is influenced by the social context they operate within [17].

Interviews with 37 stroke survivors who had previously completed a self-management intervention delivered in a group setting offered insight into the numerous benefits of peer support [18]. These included normalisation of one’s situation through the sharing of experiences, a source of motivation, and the opportunity to learn from others. To explore this further, 14 stroke survivors with no experience of group self-management interventions were interviewed. Although the concept of group self-management interventions was acceptable to stroke survivors, and seen to have potential benefits, ensuring the intervention remained tailored was an area of concern. To advance the field of stroke self-management, an intervention based on self-efficacy, which enables peer support and has the flexibility to remain tailored, is required.

Bridges meets two out of three of these criteria, but one-to-one delivery does not maximise the opportunity for peer support. Thus, there is interest in whether it could be adapted to a group setting. Further development of Bridges has been encouraged and in a recent paper was conceptualised as a ‘boundary object’, emphasising that it is constantly evolving in nature [10]. However, it is currently unknown whether Bridges would be feasible or effective if delivered in a group setting. Prior to examining efficacy, it is important to establish whether Bridges *could* be adapted for this purpose. This type of work is defined by National Institute for Health Research (NIHR) as feasibility [19] and provides parameters essential for future work.

This paper will present the protocol for research designed to address the question: is it feasible to deliver Bridges self-management as a group intervention?

### Sub questions

In order to address whether it is feasible to deliver the Bridges self-management intervention in a group setting, the following specific sub questions will be addressed:How many stroke survivors are eligible for the group self-management intervention and how quickly can they be recruited?Are participants willing to be randomised to a waitlist control in a group self-management study?What will the level of adherence and attendance to the group self-management intervention be?What will follow-up response rates to questionnaires be?How acceptable to stroke survivors is it to deliver Bridges in a group setting?How acceptable is it to family/friends/carers to deliver Bridges in a group setting?What is the magnitude and variability of change in outcome measures post intervention?

## Methods

The Standard Protocol Items: Recommendations for Interventional Trials (SPIRIT) checklist was used to ensure relevant data was reported in this protocol [20]. In addition, relevant guidelines were followed including the Medical Research Council (MRC) guidelines for complex interventions [21], Template for Intervention Description and Replication (TiDieR) guidelines for intervention descriptions [22], SPIRIT reporting guidelines [20] and NIHR advice on feasibility studies [19]. This is the first published version of the study protocol (11.04.2017).

### Approvals

Ethical approval has been obtained for this study (see the ‘Ethics approval and consent to participate’ section). The study is registered on the ISRCTN registry (ISRCTN19867168) on 20.12.2016. This study is funded by NIHR who peer reviewed the study (see the ‘Funding’ section).

### Study design

The study is designed in accordance with the guidelines listed above to answer the question: is it feasible to deliver the Bridges self-management intervention in a group setting? As recommended by guidelines, the study will use a mixed method approach [23]. A randomised waitlist control design will be used and stroke participants will be recruited to the intervention (see Table 1) at different time points. This design will allow comparison between the intervention and waitlist groups (between subjects) and pre-post intervention measures (within subjects). The former will allow sample size calculations to be made. Outcome measures (described in more detail below) collected post intervention also allow any long-term effects of the intervention to be assessed. Once the intervention has been delivered, interviews will be conducted with a sample of the research participants and focus groups will be held with family and friends. Any changes to the protocol are to be discussed with the funders, ethics committee and management panel. A SPIRIT diagram illustrating the course of the study is shown in Table 1.

**Table 1 Tab1:**
[figure not shown]
Standard Protocol Items: Recommendations for Interventional Trials (SPIRIT) diagram illustrating study design

### Recruitment

#### Sample size

The National Institute for Health Research guidelines state no formal power calculation is needed for feasibility studies such as this one [19]. Our sample size is based on published guidance for feasibility studies which varies in recommendation from 24 to 50 participants [24, 25]. We have based our sample size on the most conservative estimate for group size (*N* ≥ 50). Adherence to Bridges on a one-to-one level has been reported at 100% [26]. Dropout rates from group Bridges may be different, but this is currently unknown. A conservative estimate of 10 dropouts gave a total sample size of 60 participants.

#### Stroke survivors

Recruitment will be overseen by a Clinical Research Network. The setting will be a Hyper Acute Stroke Unit (HASU) in a central London Hospital. The intense nature of HASU means patients are initially consented to a Permission To Contact register (PTC) and given information about the study, allowing individuals to read the information sheet in their own time. The PTC is a list of those who have given permission to be contacted by researchers in the future. It enables access to a naturally occurring sample within the stroke population which minimises the risk of selection bias and maximises the chance the sample is representative of the target population. The PTC has been recruiting stroke survivors since 2013. As a result, it contains individuals who had their stroke up to 2 years previously, offering a greater range of time post stroke than if recruiting from the start of this research. A limitation of the PTC used for the proposed study is that it only comprises patients who can consent for themselves during their stay in HASU so may result in a sample of individuals with less severe strokes. This will be acknowledged in the final analysis and write up of findings.

After December 2015, the PTC was adapted to become the PTC+ which does include patients that are unable to consent for themselves (a family of friend can consent on their behalf). This could minimise a possible selection bias towards participants with less severe strokes. To gain the benefits of both these registers, we will recruit from the PTC for the first 15 participants and the PTC+ for the remaining 45. Recruitment will start from the first entry on each register and continued in chronological order. A member of the research team will enrol participants in the study (including consent). Once an individual has been enrolled by a member of the research team, they will be randomly allocated to a condition by a statistician using blocked randomisation to ensure balanced numbers. The first patient was enrolled on 25/02/2016. Question 1 (how many stroke survivors are eligible for the group self-management intervention and how quickly can they be recruited?) will be answered through documentation of this recruitment process.

#### Inclusion and exclusion criteria

As this work is feasibility, the exclusion criteria are kept broad to gain insight into who the group self-management intervention may be appropriate for. For example, it is unknown whether the group self-management intervention would be accessible for people with aphasia so this was not an exclusion criterion.*Inclusion criteria* are as follows:Confirmed diagnosis of stroke from medical professionalAble to understand a two-stage command at time of consent either verbally or non-verballyAble to understand English (no interpreter is available but participants would be encouraged to come with a family or friend supporter who could assist with interpretation)At least 18 years oldDischarged from community rehabilitation services*Exclusion criteria* are as follows:Any previous access or support from Bridges self-management interventionSevere aphasia defined as being unable to follow a two-step commandClinical diagnosis of depression from medical professionalSevere co-morbidities such as malignancy or unstable cardiovascular conditionUnable to hold a conversation in English and no supporter/friend available to translate

#### Randomisation

Participants will be randomised by a member of the research team using a blocked randomisation chart created by the statistician on the management panel (GB). Blocked randomisation was chosen as it ensured balanced numbers were allocated to the intervention and the control group, something pure randomisation cannot provide [36]. The randomisation process was unblinded, as researchers knew which condition the participants would be allocated to.

#### Family, friends and carers

Question 6 (how acceptable is it to family/friends/carers to deliver Bridges in a group setting?) will be answered by inviting family/friends/carers who accompanied a stroke survivor to the group self-management intervention to take part in a focus group. Recruitment will be determined by purposeful sampling to ensure a range of demographics such as age, gender and ethnicity, which group the individual attended, whether they had aphasia and time post stroke. Every carer who attends the group will be invited to take part in a focus group. We will aim for a minimum of four and maximum of 12 carers for each focus group.

### Intervention group

Individuals randomised to the intervention group by a statistician will complete the intervention as soon as they are enrolled. The intervention consists of four consecutive sessions over 4 weeks. They will complete baseline measures before the intervention starts and prior to randomisation. Demographic information will be gathered at baseline for all participants which included age, gender, date of stroke, co-morbidity, aphasia, living situation, ethnicity and employment status. Once they finish the intervention, they will complete outcome measures at three time points: at the end of intervention and then at 2 weeks and 6 months post intervention. Participants may withdraw from the intervention group at any time if they request to do so.

The intervention is a group self-management intervention for stroke which was adapted from the existing one-to-one Bridges self-management intervention. It was designed over a 12-month period (February 2015–February 2016). Five sources were consulted to facilitate the adaption process as follows:MRC guidelines for complex interventions [23]A systematic review of current group self-management interventions (currently unpublished) explored the key features and role of peer support which in turn informed content and structureThe existing Bridges self-management intervention [15] provided core principles and insight to potential challenges that may present during the delivery of the intervention. Also, a Bridges workbook was given to all participants (see Table 1).Interviews with stroke survivors about group self-management interventions [27] provided insights including the need for a group intervention to remain tailored, be in an accessible venue and suggested the addition of a stroke survivor joint-facilitatorA focus group with stroke survivors exploring desirable content. The focus group was made up of seven stroke survivors and one young carer and was facilitated by FJ, the founder of Bridges. Insights such as how to present the group and the need for a separate time for socialising were given.

The resulting group self-management intervention is described in Table 2 using headings suggested by guidelines [22].

**Table 2 Tab2:** Intervention reporting in line with the Template for Intervention Description and Replication (TiDieR) guidelines

Name	Group self-management intervention for stroke
Why (rationale)	Described above in the ‘Background’ section.
What (materials)	Stroke survivors will receive a user held Bridges workbook which they can take away with them and work through at their own pace. The layout and content of the workbook has vignettes, pictures and experiences from other stroke survivors. It was designed with stroke survivors and has been reviewed by Connect (communications charity). Family and friends will receive a Bridges family and friends booklet containing information about SM, stories from families living with stroke, the five top tips for supporting target setting and finally, resources and contacts. Both are available through Bridges [15]. In addition, flip chart paper, post it notes and pens may be needed to capture discussions and facilitate communication with aphasic individuals. Flipchart paper, pens.
Procedures	Participants are contacted 2 days before each session to check if they are attending. The protocol content was design using the core Bridges principles (see the ‘Core concepts of the intervention’ section). The content aims to incorporate these principles over the 4 weeks. Outcome measures are completed at the end of the fourth session.
Who provided	Each group should have the same three facilitators for each session. One stroke survivor, who will provide empathy and insight as they have experienced a stroke themselves. One speech and language therapist trained in Bridges who will provide self-management support and expertise in communication difficulties such as aphasia. Finally, one facilitator trained in Bridges providing self-management support. In this case, the latter is a PhD student and trainee health psychologist. Bridges training is one full day followed by a half day a few months later. The first day aims to help individuals build, evaluate and sustain a self-management approach with a focus on person-centred care. The second day allows individuals to reflect on their new practices, enabling the sharing of ideas and collective problem solving, as well as refreshing individuals on the core principles.
How (delivery)	Face-to-face in a group setting.
Where	The intervention will be run in community venues that are as convenient for each group member as possible.
When and how much	A four-part intervention running once a week for 4 weeks. Each session lasts 2 h and includes a break in the middle.
Tailoring	The intervention is tailored to the individual. For example, through individual goal setting and decision making. In addition, discussion topics are participant led ensuring they are relevant to those involved.
Modifications	Although there are clear time frames and content listed in the session plans, they are meant as a guideline and thus should be used flexibly in practice. For example, the order of events may vary and some aspects may be adapted to fit different contexts.
How well (fidelity)	Observations of the intervention will be carried out which will be cross referenced to the core principles of Bridges *and the original session plan*. This will enable an assessment of fidelity to the intervention protocol.

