#### Group size

There is differing literature on suggested group size. The Chronic Disease Self-Management Program (CDSMP) has 10 to 15 [28] participants in each group whereas psycho education groups suggesting five to ten [29]. For this group self-management intervention, the group size will be conservative, five to eight stroke survivors. This accounts for the complex nature of stroke. For example, those with aphasia may require the use of additional communication techniques. Family and friends are welcome to attend the sessions.

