### Waitlist group

The waitlist control group will not receive any interaction with the research team during the 6-month wait period. Participants in this condition will complete baseline measures at the start and the end of the waitlist period before randomisation as well as completing questions about demographics as specified above. They will continue to engage with usual care as they would if not taking part in research. Once the wait period is completed, they will take part in the intervention. Outcome measures for this group will be completed at the end of the intervention and again at 2 weeks post intervention. For both the intervention and the waitlist group, questions 2 (what will the level of adherence and attendance to the group self-management intervention be?) and 3 (what will follow-up response rates to questionnaires be?) will be answered using documentation of attendance to the intervention and the return rate of follow-up questionnaires. Participants may withdraw from the waitlist group at any time if they request to do so.

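### The intervention arm cannot start on enrolment when people are allocated singly but treated in groups of five to eight, so the gap between baseline and first session is uncontrolled

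*Protocol article*

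**What the plan says.** Under Intervention group, the protocol article states that those randomised to this arm "will complete the intervention as soon as they are enrolled". On baseline, the same section says "They will complete baseline measures before the intervention starts and prior to randomisation". Treatment is a fixed course: "The intervention consists of four consecutive sessions over 4 weeks". Outcomes are then collected "at the end of intervention and then at 2 weeks and 6 months post intervention".

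Under Recruitment, Stroke survivors, allocation is by person and follows enrolment: "Once an individual has been enrolled by a member of the research team, they will be randomly allocated to a condition". The Study design section describes recruitment as staggered over time. Under Randomisation, blocking was chosen because "it ensured balanced numbers were allocated to the intervention and the control group". Under Group size, "the group size will be conservative, five to eight stroke survivors".

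Under Waitlist group, controls "will not receive any interaction with the research team during the 6-month wait period". They are measured at the start and again at the end of that wait, and only then treated.

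**The concern.** A group programme with a minimum of five members cannot begin for one person on the day that person joins. If people arrive one by one and about every second one goes to the waitlist, the early members of each intervention group must wait for the later ones. Their baseline has already been taken, because it precedes randomisation. No section shown repeats it before session 1, whereas the waitlist arm does get a fresh measurement at the end of its wait.

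The quantity at stake is the within-arm pre-post change in Question 7, both its mean and its spread. Recovery, decline or life events between baseline and session 1 would be counted as change over the intervention, over an interval that differs from member to member. The Analysis and Discussion sections say that variability in the outcome measures will feed the power calculation for a larger trial. A secondary matter is that people who leave while a group fills could be read as poor adherence, and the Discussion expects adherence above 85% for progression.

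**Working it through.** **Inputs from the protocol article.** Total sample size 60, which reproduces from the Sample size section as 50 + 10. Group size g = 5 to 8. Balanced blocks, taken as 1:1, so 60/2 = 30 per arm. Course length 4 weeks, about 1 month. Waitlist period 6 months.

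**Input not in the document.** The recruitment rate, which is itself a study result under Question 1. I assume that all 60 are recruited evenly over T months, with T from 2 to 24.

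**Enrolments needed.** One intervention group takes about 2g enrolments: 2 × 5 = 10 to 2 × 8 = 16. From the first to the last member of a group there are about 2(g − 1) further enrolments: 8 to 14. Thirty people make 30/8 = 3.75 (so 4) to 30/5 = 6 groups.

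**Waiting time.** The intervention arm accrues r = 30/T people a month. The first member of a group waits (g − 1)/r, and the mean wait is (g − 1)/(2r).

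| T (months) | r per month | g = 5: mean / first (months) | g = 8: mean / first (months) |
|---|---|---|---|
| 2 | 15 | 0.13 / 0.27 | 0.23 / 0.47 |
| 6 | 5 | 0.4 / 0.8 | 0.7 / 1.4 |
| 12 | 2.5 | 0.8 / 1.6 | 1.4 / 2.8 |
| 18 | 1.67 | 1.2 / 2.4 | 2.1 / 4.2 |
| 24 | 1.25 | 1.6 / 3.2 | 2.8 / 5.6 |

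A simulation agrees (4,000 runs, random arrival times, permuted blocks of 4 assumed, groups filled in order of allocation). At T = 12 it gives a mean wait of 0.79 months and a first-member wait of 1.57 for g = 5, and 1.34 and 2.69 for g = 8. The standard deviation of the wait between people is 0.69 and 1.02 months.

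**What this does to the pre-post change.** Suppose, for illustration, that an untreated score drifts by b points a month. The mean change absorbs b × (mean wait), and its variance gains b² × (variance of the wait). At T = 12 that is 0.8b to 1.4b on the mean, and 0.69² = 0.48 to 1.02² = 1.04 times b² on the variance. The document gives no value for b, so the effect cannot be put in scale points.

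**What this does to the comparison with the waitlist.** With a wait of D months, the end-of-intervention measure falls about D + 1 months after baseline and the later one at about D + 7. The waitlist's end-of-wait measure is at 6. In most of these cases delay brings the first closer to 6, and it moves the second further away, so there is no single direction. The waitlist is untreated at its end-of-wait measure, and every intervention-arm outcome is taken after treatment.

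**The case against.** The strongest reply is that the phrase only means a prompt start. The registers already exist (one has recruited since 2013, the other dates from after December 2015) and are worked through in order, so people could be contacted in waves and a group filled within days or weeks. Staggered recruitment is compatible with that. Table 1, the schedule diagram, is not shown, and an article may leave group-filling rules and visit windows to the full protocol. This stands as a limit on the size of the problem and on any claim that a repeat baseline is absent from the study. It does not reconcile the stated sequence of individual allocation, baseline before randomisation and groups of five to eight with an immediate start.

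It is also fair that this is a feasibility study with no primary outcome, whose Question 7 results are labelled preliminary. Participants have already left community rehabilitation, so drift may be slow. Natural change also occurs in the waitlist arm, so the exposed quantity is mainly the uncontrolled within-arm change. Non-attenders can be identified, since session attendance is monitored and non-completers are asked why; the adherence point is therefore about how losses are reported.

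A reader might infer that early members of the immediate arm are in effect on a waiting list, so that the contrast with the control arm shrinks. The documents do not support this. Controls remain untreated up to their end-of-wait measure, and intervention outcomes follow treatment. The waitlist must also be formed into groups, so its start may slip by a similar amount and leave the gap in start times much as it was.

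**Conclusion.** The point holds as a conflict within the stated sequence, with a modest consequence. An immediate start is not possible for most of the intervention arm if people accrue one at a time. The interval from baseline to session 1, and from randomisation to the end-of-intervention measure, therefore varies within each group and is not fixed in the text shown.

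The size rests wholly on the assumed recruitment period and even 1:1 accrual: a mean wait of about 0.1 to 2.8 months, and about 0.3 to 5.6 months for the first member. At 12 months' recruitment, the mean wait of 0.8 to 1.4 months is similar to the length of the course itself. Recruitment in waves would bring it near the bottom of the range. The harm is to the interpretation of the within-arm change and its standard deviation. No powered test is affected, and no dilution of the between-arm contrast is established. Confidence is high for the conflict and moderate for its practical importance.

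**What to change.** Consent people individually, but take baseline and randomise in batches. Once about 10 to 16 consented people are available and a group date is set, take all baselines and randomise the batch shortly before session 1, and start the waitlist's 6-month clock on the same day. Choose batch sizes that fit the block size so that each arm receives enough people for a group. Reword the sentence on starting at enrolment to match.

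If batch randomisation is not adopted, tie the start to the next available group and repeat the four questionnaires just before session 1 in the intervention arm. Use that score as the pre value for the within-arm change only. Keep the pre-randomisation baseline as the covariate in the between-arm ANCOVA, because a score taken after allocation in one arm is not a valid common baseline.

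In either case, record the consent-to-session-1 and baseline-to-session-1 intervals, and report losses before session 1 separately from session adherence.

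The cost is protocol wording and a change in when the existing randomisation chart is used, with no extra participants. The fallback adds one questionnaire round in one arm. The downside of batching is that the wait moves to between consent and randomisation, where a few people may leave; those losses come before allocation and so cannot bias the comparison of the arms.
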